### Abstract

#### Background

Counseling supporting HIV self-testing (HIVST) users is essential to ensure support and linkage to care among men who have sex with men (MSM). An HIVST service with online real-time instruction, pre-test and post-test counseling provided by trained administrators (HIVST-OIC) was developed by previous projects. Although the HIVST-OIC was highly effective in increasing HIVST uptake and the proportion of HIVST users receiving counseling along with testing, it required intensive resources to implement and sustain. The service capacity of HIVST-OIC cannot meet the increasing demands of HIVST.

#### Objectives

The primary objective of this randomized controlled trial (RCT) is to establish whether HIVST-Chatbot, an innovative HIVST service with online real-time instruction and counseling provided by a fully automated Chatbot, would produce effects that are similar to HIVST-OIC in increasing HIVST uptake and proportion of HIVST users receiving counseling alongside testing among MSM within a six-month follow-up period.

#### Methods

A parallel-group non-inferiority RCT will be conducted. Participants are Chinese-speaking MSM aged 18 years or above with access to live-chat applications. A total of 528 participants will be recruited through multiple sources, including outreach in gay venues, online advertisement, and peer referral. After completing the baseline telephone survey, participants will be randomized evenly into the intervention or control groups. Participants in the intervention group will watch an online video promoting HIVST-Chatbot and receive a free HIVST kit. The Chatbot will contact the participant to implement HIVST and provide standard-of-care and real-time pre-test and post-test counseling, and instruction on how to use the HIVST kit through WhatsApp. Participants in the control group will watch an online video promoting HIVST-OIC and receive a free HIVST kit in the same manner. Upon appointment, a trained testing administrator will implement HIVST and provide standard-of-care and real-time pre-test and post-test counseling and instruction on how to use the HIVST kit through live-chat applications. All participants will complete a telephone follow-up survey six months after the baseline. The primary outcomes are HIVST uptake and the proportion of HIVST users receiving counseling support along with testing in the past six months measured at Month 6. Secondary outcomes include sexual risk behaviors and uptake of HIV testing other than HIVST during the follow-up period. Intention-to-treat analysis will be used.

#### Results

Recruitment and enrollment of participants will start in April 2023.

#### Conclusion

This study will generate important research and policy implications regarding using Chatbot in HIVST services. If HIVST-Chatbot is proven non-inferior to HIVST-OIC, it can be easily integrated into existing HIVST services in Hong Kong. The coverage of HIV testing and the level of support to HIVST users will be increased.

#### Trial Registration

ClinicalTrial.gov (number NCT05796622);

<https://clinicaltrials.gov/ct2/show/NCT05796622?term=NCT05796622&draw=2&rank=1>

**Keywords:** HIV self-testing, Chatbot, men who have sex with men, counseling, non-inferiority randomized controlled trial

## Introduction

## Background

Globally, the HIV epidemic among men who have sex with men (MSM) remains out of control. High coverage of HIV testing among the at-risk population is the first and crucial step to achieving the 90-90-90 targets set by the joint United Nations Program on HIV/AIDS (UNAIDS). Therefore, international health authorities recommend that MSM take up HIV testing every six months. However, despite the high risk of HIV infection among MSM in the Hong Kong Special Administrative Region (SAR) of China (HIV prevalence: 6.54% in 2017), their HIV testing rate remained inadequate (65% in the past year).

HIV self-testing (HIVST) could remove the obstacles of HIV testing faced by MSM, such as inconvenience and perceived stigma from service providers. A systematic review and meta-analysis suggested that HIVST could significantly increase the frequency and coverage of HIV testing among MSM. Therefore, the World Health Organization (WHO) strongly recommends that HIVST should be offered as an additional approach to existing HIV testing services. MSM in Hong Kong mainly relied on facility-based HIV testing and counseling provided by community-based organizations (CBO) and governmental clinics. During the COVID-19 pandemic, facility-based HIV testing services provided by CBOs and governmental clinics were suspended or closed in Hong Kong. However, the availability of HIVST kits in Hong Kong was not affected by the pandemic. An increasing demand for HIVST among MSM was observed in Hong Kong.

Pre-test and post-test counseling are essential for HIVST, facilitating linkage to care and behavioral change among HIVST users. In standard-of-care HIV testing and counseling (HTC), the pre-testing counseling involves assessing the individual's risks, providing information about HIV testing, asserting the user's right to refuse the test, and informing the user about the possibility of beneficial disclosure of sero-status status, as well as providing preventive information and material. Post-test counseling entails interpreting testing results, offering psychological support to individuals with positive results, facilitating beneficial disclosure of positive sero-status, and referring individuals for further care, treatment, and support services. Additionally, preventive information and material are provided for those with negative test results. Despite the advantages of HIVST, HIVST users may skip pre-testing or post-test counseling. There are concerns about incorrect procedures, inadequate support for users, and potential issues related to the linkage of care. A meta-analysis study examined that HIVST reduced linkage to care by 47% comparing facility-based HIV testing due to the lack of counseling support.

In previous projects, an evidence-based HIVST service was developed for MSM in Hong Kong, which included online promotion of HIVST, delivery of free HIVST kits, and provision of online real-time instruction and standard-of-care pre-test/post-test counseling via live chat application (HIVST-OIC). The HIVST-OIC is highly effective in increasing HIVST uptake and the proportion of HIVST users receiving counseling along with testing. A randomized controlled trial (RCT) showed that after being offered HIVST-OIC, 87.9% of participants took up HIVST, and all HIVST users received counseling. Moreover, the HIVST-OIC was effective in reducing sexual risk behaviors among users. The Centre for Disease Control and Prevention (CDC) listed HIVST-OIC as an evidence-based intervention and best practice. However, there are issues during the implementation, as HIVST-OIC requires intensive resources. Therefore, it is difficult to increase the service capacity of HIVST-OIC, resulting in a significant gap in implementation.

A Chatbot is a computerized program that can automatically select and provide different paths of intervention according to participants' responses. The Chatbot can offer personalized, engaging, and on-demand health communication. With the advance in artificial intelligence, a Chatbot can learn from previous human-machine interactions to increase the accuracy and quality of future interactions. A recent systematic review demonstrated the feasibility and effectiveness of Chatbot in promoting healthy lifestyles, smoking

cessation, treatment adherence, and substance misuse. The Chatbot is potentially useful for delivering real-time counseling to support HIVST users. To our knowledge, this approach is novel.

## Objectives

This study aims to demonstrate whether an innovative HIVST service with online real-time instruction and counseling provided by a fully automated Chatbot (HIVST-Chatbot) is as efficacious, if not more efficacious, as HIVST-OIC in increasing HIVST uptake and the proportion of HIVST users receiving counseling alongside testing among MSM in Hong Kong.

The primary objective is to establish whether HIVST-Chatbot would produce effects similar to HIVST-OIC in increasing HIVST uptake and the proportion of HIVST users receiving counseling alongside testing within a six-month follow-up period. We hypothesize that HIVST-Chatbot would be statistically non-inferior to HIVST-OIC in increasing HIVST uptake and the proportion of HIVST users receiving counseling alongside testing. The non-inferiority margin is set as 10% (HIVST-Chatbot is no worse than 10% less than that of the HIVST-OIC). The secondary objectives are to compare HIVST-Chatbot with HIVST-OIC on the prevalence of condomless anal intercourse (CAI), multiple male sex partnerships, and uptake of HIV testing other than HIVST at Month 6.

## Methods

### Study design

A parallel-group non-inferiority randomized controlled trial will be conducted. A total of 528 participants are randomized 1:1 to either the intervention group (n=264) or the control group (n=264). We will promote and implement HIVST-Chatbot and HIVST-OIC in the intervention group and control group, respectively. A telephone follow-up evaluation will be conducted six months after the baseline survey by blinded interviewers. The study was registered at ClinicalTrial.gov (number NCT05796622). A flowchart diagram is shown in Figure 1.

[figure not shown]

**Figure 1. Flowchart diagram for the non-inferiority randomized controlled trial**

### Participants and recruitments

Inclusion criteria are 1) Hong Kong Chinese-speaking men aged at least 18 years old, 2) anal intercourse with at

least one man within the last six months, 3) willing to provide contact information for follow-up at Month 6, (4) having access to WhatsApp, and 5) without intention to leave Hong Kong for one month consecutively in the next six months. Those who have been diagnosed as HIV-positive will be excluded.

Participants will be recruited through multiple sources. Upon obtaining the approval of the owners, trained and experienced fieldworkers will approach prospective MSM participants in gay bars and saunas at different timeslots during weekdays and weekends. They will brief prospective participants about the study details and give them an information sheet. The research team will also conduct online outreach by posting study information periodically as discussion topics on gay websites with the highest traffic in Hong Kong. If prospective participants are interested in this study, they can contact the research team through private messaging, WhatsApp, telephone, or email. Recruitment will be supplemented by peer referrals. Participants will be guaranteed anonymity during the study, the right to quit at any time, and that refusal will have no consequences. Verbal instead of written informed consent will be obtained to allow participants to maintain anonymity. Fieldworkers will sign a form pledging that the participants have been fully informed about the study. Similar methods to obtain informed consent have been commonly used in interventional studies targeting MSM in Hong Kong. Multiple forms of contact information will be obtained to make an appointment for a baseline telephone survey, which takes about 20 minutes to complete. Another telephone follow-up survey will be conducted six months after the completion of the baseline survey. A supermarket coupon (HK\$50) will be mailed to an address provided by the participants upon completion of each survey. Ethics approval was obtained from the Survey and Behavioral Research Ethics Committee of the Chinese University of Hong Kong (Ref#: SBRE-22-0488).

### **Sample size planning**

The target sample size is 528 (264 per group). Our previous study showed that about 90% of MSM used HIVST after exposure to HIVST-OIC promotion and implementation. We conservatively assume that 80% of participants in the control group will take up HIVST during the project period. A non-inferiority margin of between-group difference of this primary outcome is set at 10% (no worse than 10% less than that of the control group). A sample size of 198 per group will be sufficient to confer 80% power at the one-sided significance level of 0.05 (PASS 11.0). Given the 25% drop-out rate during the follow-up period, 264 participants per group (528 total) will be needed for the study.

### **The baseline survey and random allocation process**

Participants will be randomized evenly to either the intervention or control groups. Computer-generated random allocation codes will be produced and sealed in opaque envelopes by a research staff member without involvement in recruitment or baseline survey. One envelope will be drawn and opened by the fieldworkers. They will then inform the participant which group he is assigned to. Block randomization with a block size of eight will be used.

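### A single block size of eight, with unblinded fieldworkers opening the envelopes, could let field staff infer some upcoming allocations (20% with certainty at most)

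*Protocol*

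**What the plan says.** The Protocol section *The baseline survey and random allocation process* sets one block size: "Block randomization with a block size of eight will be used". The codes are computer-generated and "sealed in opaque envelopes by a research staff member without involvement in recruitment or baseline survey". At the point of allocation, "One envelope will be drawn and opened by the fieldworkers", and "They will then inform the participant which group he is assigned to".

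*Participants and recruitments* gives the same staff group a recruiting role: "trained and experienced fieldworkers will approach prospective MSM participants in gay bars and saunas". It also has them document consent: "Fieldworkers will sign a form pledging that the participants have been fully informed about the study". The other routes into the trial are online outreach by the research team and peer referral. The baseline telephone survey is booked by appointment, and the Abstract (*Methods*) places randomization after that survey. *Study design* gives 264 men per group, 528 in total, and describes only the Month 6 interviewers as blinded.

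The Protocol does not say whether the block size is withheld from fieldworkers, whether there is one sequence or several, or whether envelopes are numbered and taken in order.

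**The concern.** Within a balanced block of known length, each opened envelope carries information about those still sealed. The last place in every block is fully determined, and earlier places often are. Fieldworkers learn every allocation they open, so the group that recruits in venues also builds up the allocation history. The Protocol keeps the person who prepares the codes apart from recruitment, but does not extend that separation to those who open the envelopes.

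Someone who can foresee the next group can influence, deliberately or not, whom to approach or when to book a baseline survey. The arms could then differ in readiness to test, which bears directly on the primary outcome of HIVST uptake. The planned adjustment (*Statistical analysis*) covers only baseline variables with P < .05. The variables listed under *Baseline background characteristics* include history of HIV testing but no measure of motivation to test, so adjustment would be partial.

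**Working it through.** **Inputs.** Block size 8 and 1:1 allocation (four places per arm in each block) come from the randomization section and *Study design*. The total is 528, so 528 / 8 = 66 complete blocks. The observer is assumed to know the block size and the block start and to have seen every earlier allocation in one ordered sequence. The Protocol confirms none of these three conditions, so the results are upper bounds.

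**The plan's own figure.** The Protocol gives no figure for predictability. Its sample size reproduces: 80% uptake in both arms, a 10-point margin, one-sided 0.05 and 80% power give (1.645 + 0.842)² × 2 × 0.8 × 0.2 / 0.1² ≈ 198 per group, and 198 / 0.75 = 264. This point does not affect it.

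**Allocations known with certainty.** A place is certain once one arm is used up, that is, when all remaining places belong to the same arm.
- Place 8: always, probability 1
- Place 7: 2 × (4×3)/(8×7) = 3/7
- Place 6: 2 × (4×3×2)/(8×7×6) = 1/7
- Place 5: 2 × (4×3×2×1)/(8×7×6×5) = 1/35

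The sum is 56/35 = 1.6 per block, and 1.6 / 8 = 20%. Over the trial, 66 × 1.6 = 105.6, about 106 of 528. Enumerating all 70 orderings of a 4+4 block gives the same result. It also shows that 27.5% of allocations can be called with probability of at least 75%.

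**Best guessing.** The observer always guesses the arm with more places left, and a tie counts as one half. With h = 4 places per arm, the expected number correct per block is h + ½ × [2^(2h) / C(2h, h) − 1] = 4 + ½ × (256/70 − 1) = 5.329. Then 5.329 / 8 = 66.6%, against 50% by chance. Over 528 allocations that is 528 × 0.1661 ≈ 88 extra correct guesses.

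**Effect of varying the block size.** This was simulated with 200 trials of 528 per set. The observer knows the set of sizes and the full history and updates by Bayes' rule.

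| Block sizes | Certain | Best guess correct |
|---|---|---|
| Fixed 8 (exact) | 20.0% | 66.6% |
| 4, 6, 8 | 2.3% | 68.0% |
| 6, 8, 10 | 1.6% | 66.5% |
| 4, 8, 12 | 3.0% | 66.1% |

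Varying the size removes most of the certainty and leaves partial guessing where it was. Partial guessing falls only if those who recruit and book do not see the allocation history.

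**Possible effect on the estimate (illustration only).** Let d be the uptake gap between more and less motivated men, assumed to be 5 to 20 points, and assume complete steering. Steering on the certain places shifts the between-group difference by up to 0.20 × d, or 1.0 to 4.0 points in either direction, against a margin of 10 points. The Protocol gives no value for d and no evidence that steering would happen.

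**The case against.** The strongest case against is that the plan has real safeguards and that the figures describe a worst case. The codes are computer-generated and sealed in opaque envelopes by someone outside recruitment, so nobody can read the next envelope. Eligibility and baseline data precede the draw, so selection would have to act earlier, through whom to approach or when to book, with the block position foreseen across the gap. All of this stands. It narrows the opportunity, but none of it prevents inference from allocations already opened.

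A reader might also infer four stronger things that the Protocol does not support.
- *That upcoming allocations are generally predictable.* Even for the fully informed observer, 80% are not certain. Several fieldworkers sharing a stack without pooling, or not knowing the block size, would know less.
- *That the person who recruits a man also opens his envelope.* Both tasks fall to fieldworkers as a group, but venue outreach is one of three recruitment routes, and the Protocol does not link the individuals.
- *That fieldworkers may choose among envelopes.* The text is silent on order, and drawing one is compatible with taking the next. The two worries also exclude each other: if any envelope could be picked, the block order would be lost and the 20% and 66.6% would not apply.
- *That the bias would favour the Chatbot and hide inferiority.* The Protocol shows no incentive in that direction, and steering the other way would make non-inferiority harder to show.

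**Conclusion.** The point holds as an avoidable weakness in allocation concealment. It is not evidence that allocation will be compromised. A single fixed block size, combined with unblinded fieldworkers who open the envelopes and belong to the staff group that recruits in venues, could let some upcoming allocations be inferred. The ceiling is 20% certain (about 106 of 528) and 66.6% correct by best guess. It rests on a known block size, known block starts and one fully observed ordered sequence. The true figure could be much lower, and the direction of any resulting bias is unknown. The sample size is unaffected. The change is worth making because it is cheap and uses staff the Protocol already names.

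**What to change.** 1. Replace the fixed block of eight with randomly varying block sizes, for example 4, 6 and 8, and do not disclose them to field staff. This takes certain allocations from 20% to about 2%.
2. Because best guessing would stay near 68%, also have the staff member who prepared the codes, who is not involved in recruitment, release each allocation strictly in list order and only once the baseline survey is complete. Keep the running allocation history from those who recruit and book surveys. Where possible, whoever tells participants their group should be someone else.
3. If envelopes are kept, number them sequentially and open them in order, with the date and time logged. State in the Protocol that this is the procedure.

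The cost is a new list, a few sentences of procedure and one small logistical step per participant. Arm sizes may end slightly unequal: 528 is exactly 66 blocks of eight, whereas a varying sequence may stop inside a block. With a largest block of eight, the difference is then at most four participants.

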### **The control group**

#### ***Online promotion of HIVST-OIC***

Participants will watch a 7-minute online video promoting HIV testing in general and HIVST-OIC developed by previous projects. The online video is based on the constructs of perceived benefits and perceived barriers of the Health Belief Model. The video has two parts. The first part is to promote HIV testing in general. A local MSM introduces the potential benefits of taking up HIV testing in general (e.g., help to detect HIV infection earlier, increase trust between sex partners and reduce psychological burdens) and the WHO recommendation for MSM with risk behaviors to take up HIV testing every six months. In the second part, the same MSM narratively discusses the benefits and barriers of HIVST-OIC, demonstrates its procedures, and emphasizes the availability of real-time online support.

### ***Signing up for HIVST-OIC***

After completing watching the online video, participants are asked to select their preferable HIVST kits (oral fluid-based or blood-based), choose a service model (comprehensive version with real-time instruction, pre-test, and post-test counseling, or simplified version with real-time post-test counseling only), and fill in their contact information and address to receive the HIVST kits. Participants can receive a free HIVST kit through rapid courier service, mail it in a plain envelope, or pick it up at collaborative CBO or the research office. Participants can make an appointment with trained HIV testing administrators to implement HIVST-OIC after receiving the HIVST kit. OraQuick® in-home test kit (OraSure Technologies, Inc.; sensitivity: 91.7%; specificity: 99.9%) and BioSure® HIV self-test kit (BioSure, Inc.; sensitivity: 99.7%; specificity: 99.9%) will be used in this study.

### ***Implementation of HIVST-OIC***

The implementation will follow the same procedures reported in previous studies. Through live-chat applications (e.g., Line, WhatsApp, Skype), an experienced HIV testing administrator will guide the participants through self-test procedures on-screen and in real-time. Participants are guaranteed anonymity, and no taping will be made. Users may elect to refrain from displaying their faces on the screen. Standard-of-care pre-test and post-test counseling will be provided if the user chooses the comprehensive version. The administrator will also explain how to use the HIVST kits and send the user a demonstration video if needed. The entire procedure of the comprehensive version takes about 60 minutes to complete, which is comparable to the time required for facility-based HIV testing and counseling. If the user prefers a simplified version, pre-test counseling will be replaced by online pre-test information (e.g., window period of HIVST, types of sexual behaviors with a high risk of HIV transmission). Users can access the demonstration video and standard-of-care real-time counseling. The simplified version will take about 20 minutes to complete. Users screened to be positive will be given immediate psychological support and explained about the need to take up free confirmatory HIV antibody testing offered by the Department of Health. If necessary, the collaborative CBO staff will accompany them to the CBO or Department of Health.

